**Methods:**

This randomized, double-blind, placebo-controlled trial will be performed at two centers and will include a *Banha-sasim-tang *group and placebo group. Each group will consist of 50 FD patients. Six weeks of administration of *Banha-sasim-tang *or placebo will be conducted. During the subsequent 2 months, follow-up observations of primary and secondary outcomes will be performed. The primary outcomes are differences as measured on the gastrointestinal symptom scale, and the secondary outcomes are differences as measured on the visual analogue scale for dyspepsia and on the questionnaire for FD-related quality of life. All outcomes will be measured at baseline, at 2, 4, and 6 weeks of treatment, and at the 1 and 2 month follow-up. Cutaneous electrogastrography will be performed and assessed at baseline and at 6 weeks.

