## Methods

### Objectives

The aims of this study are to:

(1) To determine whether BST can improve dyspeptic symptoms in patients with FD.

(2) To examine the relationship between dyspeptic symptoms and cutaneous EGG recordings and a possible biological evidence of BST's efficacy via cutaneous EGG recordings.

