### Hypothesis

(1) Six weeks of oral administration of BST improves dyspeptic symptoms and quality of life in patients with FD.

(2) In patients with FD or FD subtypes according to the Rome III criteria, there will be a significant correlation between the degree of dyspeptic symptoms and cutaneous EGG recordings and 6 weeks of oral administration of BST can improve the abnormal frequency and power parameters on cutaneous EGG.

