### Statistical analysis

The primary hypothesis is that oral administration of BST is more effective than placebo for treating FD. We hope to prove this hypothesis by means of a 2-sided test yielding a 5% significance level. Because there is no relevant previous study using BST for calculating sample size, we referred to a similar herbal trial for FD treatment which used the GIS scale [1]. The formula for estimating the sample size is as follows:

The previous trial demonstrated 3.5 points of improvement (*μ*_*c *_- *μ*_*t *_= *Δ*) in the GIS scale over treatment with placebo during 4 weeks of herbal treatments [1]. The same study indicated a mean standard deviation (SD = *σ*) of 5.37. In our study, the ratio (*λ*) of experimental group to placebo group will be 1:1. With a power of 80% (1 - β) and significance level of 5% (α), assuming Δ = 3.5 and σ = 5.37, a sample size of *n_t _*= *n_c _*= 37 patients per treatment group will be required. (*n_t_*, number of BST group; *n_c_*, number of placebo group). Considering an assumed dropout rate of 25%, a total of 100 patients will be needed.

The analysis strategy in this study is as follows:

As a first step, the baseline characteristics of both groups, sex, age, duration of dyspeptic periods, and smoking, will be compared. As a second step, we will compare the efficacy of BST and placebo, as the change in GIS totals from the beginning (0 day) to the end (6 weeks) of the study period. As a third step, we will analyze the secondary variables (VAS and FD-QoL) in the same manner as we did the GIS scale. Finally, various parameters in the EGG measurement, such as frequency and power-related variables will be compared before and after treatment in both groups. Correlations between changes in GIS scale results and EGG parameter findings will also be analyzed.

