All analyses in this study will be based on the intention-to-treat principle. If data distribution is skewed owing to insufficient sample size, relevant transformation by a statistician prior to analysis will be made. The baseline characteristics will be compared by either *χ*^2^-test or the Student *t*-test. Primary and secondary outcomes will be presented as means and SDs, and analyzed by independent *t*-tests, Mann-Whitney tests, or Wilcoxon singed-rank tests. Correlations between the GIS scale and EGG parameters will be analyzed by Pearson's correlation coefficients or by Spearman's Rho. Adverse events will be calculated and compared using *χ*^2^-test or Fisher's exact test.

Statistical analyses will be conducted in a blind manner by an independent statistician and performed using SPSS 16.0 (SPSS inc., Chicago, Illinois, USA).

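### The claim that BST improves EGG parameters has no stated BST-versus-placebo comparison; the plan names only a before-versus-after comparison in both groups

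*Protocol article*

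**What the plan says.** In the Protocol article, the Objectives section seeks "a possible biological evidence of BST's efficacy via cutaneous EGG recordings". The Hypothesis section states that "6 weeks of oral administration of BST can improve the abnormal frequency and power parameters on cutaneous EGG". The same objective and hypothesis have a second part, the association between symptoms and EGG recordings.

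The Statistical analysis section sets out the comparisons in order:

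- GIS: "we will compare the efficacy of BST and placebo, as the change in GIS totals".
- VAS and FD-QoL: "we will analyze the secondary variables (VAS and FD-QoL) in the same manner as we did the GIS scale".
- EGG treatment effect: "various parameters in the EGG measurement, such as frequency and power-related variables will be compared before and after treatment in both groups".
- EGG and symptoms: "Correlations between changes in GIS scale results and EGG parameter findings will also be analyzed".

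Further down, the section says that primary and secondary outcomes will be "analyzed by independent *t*-tests, Mann-Whitney tests, or Wilcoxon singed-rank tests". EGG is neither: the Outcome measures section lists GIS as primary and VAS and FD-QoL as secondary, and EGG is described separately under Measurement of GMA. The abstract gives its timing: "Cutaneous electrogastrography will be performed and assessed at baseline and at 6 weeks".

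**The concern.** The hypothesis about EGG parameters concerns an effect of BST, so it needs a contrast with placebo. The analysis named for it compares time points. A before-versus-after change in the BST arm combines any drug effect with placebo response, the effect of going through a second fasting and test-meal recording, and, for parameters that were abnormal at baseline, regression to the mean. The randomised placebo arm measures these influences, but only if the change in one arm is set formally against the change in the other. A significant change in one arm beside a non-significant change in the other is not a test of the difference between them.

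At stake is a report that BST improved gastric myoelectrical activity when both arms moved by the same amount. EGG is the subject of one of the trial's two objectives, and its treatment claim rests on this one sentence.

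**Working it through.** **1. Is a between-arm EGG comparison stated anywhere?**

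| Measure | Comparison stated | Contrast between arms? |
|---|---|---|
| GIS | BST against placebo, change from day 0 to week 6 | Yes |
| VAS, FD-QoL | As for GIS | Yes |
| EGG parameters | Before against after, in both groups | Not stated |
| EGG with GIS | Correlation (Pearson or Spearman) | No, and none is needed |

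The two between-arm tests named (independent t, Mann-Whitney) are assigned to primary and secondary outcomes, so they do not reach EGG. No test is named for EGG apart from the correlations.

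**2. Numbers per arm.** The only sample-size figure is for GIS. With Δ = 3.5, σ = 5.37, two-sided 5% and 80% power:

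n = 2 × (1.960 + 0.842)² × 5.37² / 3.5² = 36.95, rounded up to 37 per arm. Then 37 / (1 − 0.25) = 49.3, rounded up to 50 per arm, 100 in total. The stated figures reproduce. Both 37 and 50 per arm are used below.

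**3. How often could an equal change look like a BST effect?** The protocol gives no EGG effect size, SD or drift, so the shift is an assumption. Let both arms have the same true change of d SDs of the change, with no BST effect, and test each arm with a paired t-test at two-sided 5%.

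- Probability that one arm is significant: p = P(|T| > t₀.₉₇₅,ₙ₋₁), where T is non-central t with n − 1 degrees of freedom and non-centrality d√n.
- The arms are independent, so P(BST significant, placebo not) = p(1 − p).

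| d | p, n = 37 | p(1 − p), n = 37 | p, n = 50 | p(1 − p), n = 50 |
|---|---|---|---|---|
| 0.2 | 0.220 | 0.171 | 0.284 | 0.203 |
| 0.3 | 0.427 | 0.245 | 0.548 | 0.248 |
| 0.4 | 0.658 | 0.225 | 0.792 | 0.165 |
| 0.5 | 0.841 | 0.134 | 0.934 | 0.062 |

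The misleading pattern is not monotonic in d. It peaks at 0.25, where p = 0.5, and falls for large shifts because both arms become significant: at d = 0.7 it is 0.014 with 37 per arm and 0.002 with 50.

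**4. The between-arm test.** When both arms change equally, a two-sample test of the changes at two-sided 5% gives a false difference 5% of the time whatever d is. By symmetry about half of these, 2.5%, have the larger change in the BST arm. It has 80% power for a standardised difference of 0.66 with 37 per arm or 0.57 with 50.

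**The case against.** The strongest defence is that the sentence is loose rather than wrong. It does not say that each arm will be tested separately, names no paired test for EGG, and does not say that patterns of significance will be contrasted. A between-arm comparison may be intended. That is possible, but the text does not say so, and the same paragraph does say so for GIS, VAS and FD-QoL. If it was intended, the sentence still needs correcting. Nor is this a detail left to an unseen analysis plan: the article states an analysis, in a form that does not answer its own hypothesis.

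Several stronger readings are tempting and are not supported:

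- *The whole EGG aim lacks a valid analysis.* The association between symptoms and EGG has its own correlation analysis, for which before-versus-after change is a natural quantity and no arm contrast is needed.
- *The trial cannot attribute EGG changes to BST.* EGG is recorded at baseline and week 6 in randomised arms, so the design allows attribution. Only the stated analysis falls short.
- *The placebo arm is ignored.* It is analysed, since the comparison is made in both groups. What is missing is a stated contrast.
- *The p columns above are inflated type I error rates.* They are the power to detect a shift that, by assumption, really occurs in that arm. The error lies in attributing the shift to BST, and only the discordant pattern is used here as a measure of it.

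It is also fair to say that eligibility selects on GIS severity and not on EGG. Regression to the mean is therefore a direct concern mainly for parameters, or patients, singled out as abnormal at baseline, which is how the hypothesis is worded.

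**Conclusion.** The point holds for the treatment-effect part of the EGG aim. No analysis stated in the protocol tests whether EGG parameters change more on BST than on placebo.

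Under an assumed equal shift of 0.2 to 0.5 SD of the change and no BST effect, a result significant in BST and not in placebo arises about 13-25% of the time per parameter with 37 per arm, and about 6-25% with 50. A between-arm test gives a false difference in either direction about 5% of the time. These figures illustrate the risk and do not predict it: the shifts are assumed, a paired t-test is assumed, and the pattern misleads only if it is read as evidence of a BST effect. Measurement of GMA lists several parameters, so the opportunity arises more than once.

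Severity is moderate. The aim is mechanistic, and the primary GIS conclusion, the VAS and FD-QoL analyses, the sample size and the correlation analysis are untouched.

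**What to change.** Replace the EGG sentence in the Statistical analysis section with wording such as:

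> The change from baseline to week 6 in each EGG parameter will be compared between the BST and placebo groups by ANCOVA with the baseline value of that parameter as covariate, and reported as the between-group difference with its 95% CI. Before-versus-after results within each group are supportive and will not be the basis for attributing an EGG effect to BST.

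Applying the GIS method to EGG would also repair the defect. ANCOVA is preferable because it adjusts for chance differences between the arms at baseline. The correlation sentence can stay as it is.

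The cost is a change of wording, to be made before the EGG data are analysed. The data are already planned in both arms at both times, so no visits, recordings or patients are added.

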### Measurement of GMA

Gastric hypomotility and uncoordinated antral duodenal contractions in FD patients are closely associated with gastric myoelectrical dysrhythmias. These dysrhythmias arise from dysregulation of gastric slow waves, which normally occur at a frequency of 3 cycles per minute (cpm) [26].

Electrogastrogram records GMA acquired from cutaneous abdominal electrodes [27]. Although some researchers have suggested that some cutaneously acquired dysrhythmias may be artifactual in nature [28], other experiments have suggested a positive correlation between the frequencies found with cutaneous EGG recordings and myoelectrical signals acquired from gastric serosal leads [29,30].

In this study, the GMAs of the participants will be measured using surface multichannel EGG (Polygraf ID^®^, Medtronic A/S, Denmark) at baseline and at 6 weeks. This method of EGG measurement will be conducted as described previously [26]. First, the epigastric skin to be attached to the electrodes will be shaved and abraded with a sandy skin preparation jelly to reduce impedence. Four active surface electrodes will be positioned at the sites: the corpus of stomach as channel 1, proximal antrum as channel 2, distal antrum as channel 3, and pylorus region as channel 4. A ground electrode and a reference electrode will also be placed. EGG measurements will be performed in a quiet room and patients will fast over night for ≥ 8 hours. Participants will be asked not to talk and to remain as still as possible during the EGG assessment to avoid motion artifacts. Patients will undergo a 20 minute fasting (preprandial) EGG measurement in the supine position, then they will eat two scrambled medium eggs and two pieces of toasted bread with 500 ml of water as the standard solid test meal (500 Kcal). Then, postprandial EGG measurement will be conducted for 40 minutes. The percentage of slow wave coupling, the EGG dominant frequency and power, the percentage of normal gastric slow waves, the percentage of gastric dysrhythmia, and the postprandial to preprandial power ratio will be assessed.

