## Discussion

The current clinical study is a randomized, double-blind, placebo-controlled trial investigating the safety and efficacy of frequently used herbal formulas as part of the national project for studying the traditional herbal medicines of South Korea. This clinical trial belongs to the 2009 Traditional Korean Medicine R&D projects funded by the Ministry for Health & Welfare & Family Affairs, Republic of Korea. BST is one of the most frequently prescribed herbal formulas in Korea, BST is thought to be safe, and experimental evidences support BST's effectiveness for dyspepsia [18-20]. However, there have not been any randomized controlled trials showing the effectiveness of BST for the treatment of FD. Through the current study, we expect to gain objective clinical evidences of the efficacy and safety of BST for the treatment of FD.

The causes of functional dyspepsia are diverse and overlapping. Of the putative causes of FD, delayed gastric emptying/gastric dysmotility is one of the most important causes of FD in Korea and has been reported to closely correlate to GMA recorded by cutaneous EGG [5]. Because many researchers have suggested that cutaneous EGG could be a relatively easy technique that can be used to assess GMA in clinical settings and EGG recordings showed a significant correlation with dyspeptic symptoms in FD patients and changes in cutaneous EGG parameters in FD patients could reflect changes in their gastric motility and their dyspeptic symptoms [29,30], it is postulated that a significant correlation can be found between dyspeptic symptoms of FD patients and cutaneous EGG recordings in this trial, and the improvement in dyspeptic symptoms after the oral administration of BST may be assessed by measuring the changes in cutaneous EGG parameters. Correlations in these parameters can evaluate the possibility of clinical applications of cutaneous EGG in the treatment of FD, and a detailed guide, based on biological evidences, for treatment in FD patients.

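### The second hypothesis predicts a significant symptom–EGG correlation without naming the parameter, channel, meal state or direction, so its false-positive chance can lie well above 5%

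*Protocol article*

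**What the plan says.** The protocol article lists the relation between symptoms and cutaneous EGG as its second objective. Under Hypothesis, item 2 states for FD patients or FD subtypes that "there will be a significant correlation between the degree of dyspeptic symptoms and cutaneous EGG recordings". The same sentence adds a separate claim, that six weeks of the herbal formula improves abnormal EGG frequency and power.

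Measurement of GMA describes four active electrodes, each a channel, and a fasting and a fed recording. The measures are: "The percentage of slow wave coupling, the EGG dominant frequency and power, the percentage of normal gastric slow waves, the percentage of gastric dysrhythmia", plus a fed-to-fasting power ratio. That makes six parameters.

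Under Statistical analysis, EGG comes last. Frequency and power variables are given as examples of an open list, and then: "Correlations between changes in GIS scale results and EGG parameter findings will also be analyzed". Pearson or Spearman coefficients may be used, and no rule for choosing between them is given for the correlations.

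The intended use is ambitious. The abstract's Discussion says that the possibility of clinical applications will be clarified. The main Discussion says: "Correlations in these parameters can evaluate the possibility of clinical applications of cutaneous EGG in the treatment of FD". It adds that they can inform a treatment guide.

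**The concern.** A hypothesis that predicts a significant correlation, without saying of what, can be supported by any one of many pairs. Here the choice runs over parameter, channel, meal state, population (all FD, postprandial distress, epigastric pain), time point (baseline or change) and coefficient. By contrast, the article fixes its main efficacy comparison to one total score over one interval.

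What is at stake is the conclusion on EGG. It could rest on whichever pair happened to reach p < 0.05, and the pair need not be strong. In a sample of 100, p < 0.05 requires only |r| of about 0.20.

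**Working it through.** **The plan's own figure.** The article calculates a sample size only for the symptom score, "assuming Δ = 3.5 and σ = 5.37", with 80% power and 5% two-sided significance. n = 2(1.96 + 0.842)² × 5.37² / 3.5² = 2 × 7.85 × 28.84 / 12.25 = 36.95, so 37 per group. 37 / 0.75 = 49.3, so 50 per group and 100 in total. The stated figures are reproduced. The article gives no error rate or test count for the EGG correlations.

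**Inputs for the check.**
- From Measurement of GMA: six parameters, four channels, two meal states.
- From Hypothesis and Participants: up to three populations (all FD and two subtypes).
- Assumed: the 5% two-sided level stated for the primary hypothesis is also used for each EGG correlation, and no true correlation exists.

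**Test count (a construction; the article does not say how channels and meal states are combined).**
- Frequency, power, normal slow waves and dysrhythmia: 4 × 4 channels × 2 states = 32.
- Power ratio, which already combines the two states: 4 channels = 4.
- Coupling, which is not counted per channel: 2 states = 2.
- Sum: 38 per population, and 3 × 38 = 114 with both subtypes. Baseline and change together would double these.
- Lowest count considered: six, one test per parameter.

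**Independent tests.** Chance of at least one p < 0.05 is 1 − 0.95^m.
- m = 6: 1 − 0.735 = 26%.
- m = 38: 1 − 0.142 = 86%.
- m = 114: 99.7%.

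When every null is true, the expected number of false positives is 38 × 0.05 = 1.9 or 114 × 0.05 = 5.7, whatever the dependence.

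**Correlated tests.** Measures from one recording are related, so independence gives an upper figure. Simulated normal test statistics with equal pairwise correlation ρ (assumed values) give:

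| ρ | m = 6 | m = 38 | m = 114 |
|---|---|---|---|
| 0.3 | 24% | 73% | 96% |
| 0.5 | 21% | 56% | 80% |
| 0.7 | 17% | 37% | 52% |
| 0.9 | 11% | 18% | 23% |

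The last column overstates dependence, because the two subtypes are different patients.

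**Second simulation.** This used Pearson tests on 100 patients over a full 6 × 4 × 2 = 48 grid. The assumed correlations between parameters, channels and states were 0.3/0.6/0.4, 0.5/0.8/0.5 and 0.7/0.9/0.7. The chance of at least one significant pair was about 80%, 65% and 43% in all FD. It rose to 97%, 90% and 73% when two equal-sized subtypes were also tested.

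**Size needed for significance.** |r| = t / √(t² + n − 2). For n = 100: 1.984 / √(3.94 + 98) = 0.20, about 4% of variance. For 75 completers (25% dropout): 1.993 / √(3.97 + 73) = 0.23, about 5%.

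**The case against.** The strongest reply is that this is an article. The choice of channel and state, the coefficient rule and any multiplicity method commonly sit in an analysis plan or full protocol, neither of which is shown. EGG is not among the primary or secondary outcomes and is analysed last, the objective is only to examine a relationship, and the "2-sided test yielding a 5% significance level" is stated for the primary hypothesis alone. This stands in part: the absence of an adjustment method is not a finding. What remains is the hypothesis itself. It is stated formally, is not called exploratory, leaves its object and population open, and has conclusions on clinical use attached to it.

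A reader might infer more than the documents support:
- *That chance confirmation is almost certain, or that the hypothesis can hardly fail.* The 86% needs 38 independent tests, and both the count and the independence are assumed. Hypothesis 2 also has a treatment-effect part, which a chance correlation does not satisfy.
- *That any single significant pair suffices by rule.* This is the natural reading of the sentence, but no decision rule says so.
- *That changes are correlated over both arms pooled.* The article does not say which arms enter. Its abstract speaks of changes during administration of the formula.
- *That size is ignored.* Pearson and Spearman coefficients are measures of size. The weakness is that the prediction is worded as significance.

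**Conclusion.** The point holds in limited form: hypothesis 2 is too unspecific for the conclusions drawn from it. On the natural reading, every assumption tried gives a false-positive chance above 5%. It runs from 11% for six strongly correlated tests, through 18% to 73% for 38 correlated tests, to 86% for 38 independent ones, and is higher once the subtypes are added. These figures rest on a 5% level per correlation, an inferred test count, assumed inter-test correlations and no true association. The primary symptom-score comparison, its sample size and any efficacy conclusion from it are unaffected. The change is worth making because it determines what the trial may claim about EGG.

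**What to change.** Before any EGG data are examined, the sponsor names one key EGG parameter, in one channel and one meal state, for two confirmatory correlations in all FD patients: baseline EGG with baseline symptom total, and change with change. Fixing it before unblinding is not enough, because the baseline correlation needs no treatment codes and could be computed for every pair while blinded. Which parameter to choose is for the sponsor to justify; the article gives no basis for preferring one.

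Use Spearman for both, with 95% confidence intervals, and Holm across the two (smaller p against 0.025, then the larger against 0.05). State the arm handling of the change correlation: within the active arm, which matches the abstract's question but has at most 50 patients, or both arms with adjustment for arm. Label all other EGG correlations and the subtypes exploratory.

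Alternatively, label every EGG correlation exploratory and temper the statements on clinical use in the abstract and the Discussion.

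The cost is a few sentences, with no extra patients or measurements. The downside is that other EGG correlations can no longer be claimed as confirmatory.

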## Abstract

**Background:**

Functional dyspepsia (FD) is characterized by a high prevalence rate and no standard conventional treatments. Alternative therapies, such as herbal formulas, are widely used to treat FD. However, there are inadequate evidences regarding the safety and efficacy of these formulas. Moreover, the mechanisms by which herbal formulas act in the gastrointestinal tract are controversial. In traditional Korean medicine, *Banha-sasim-tang *has long been one of the most frequently prescribed herbal formulas for treating dyspepsia. The current study is designed to evaluate the efficacy and safety of *Banha-sasim-tang *for FD patients and to examine whether there will be a significant correlation between cutaneous electrogastrography recordings and dyspeptic symptoms in FD patients, and between changes in gastric myoelectrical activity and improvement in dyspeptic symptoms during *Banha-sasim-tang *administration.

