Moreover, BST can be obtained as an over-the-counter herbal formula in Korea or prescribed for dyspeptic symptoms by the Traditional Korean Medicine doctors. For that reason, reliable clinical evidence regarding BST as treatment for FD is needed. However, there are no relevant randomized controlled clinical trials regarding FD as far as we know.

The current study is designed to investigate the effect of BST on FD and related quality of life. We will also examine the relationship between the frequency or power variables in cutaneous EGG and dyspeptic symptoms of FD patients in this trial and determine whether the changes in GMA recorded by cutaneous EGG before and after the oral administration of BST can reflect the clinical efficacy of BST in the treatment of FD.

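### The planned GIS–EGG change correlation has no term for treatment arm and does not say whether the arms are pooled; if they are, arm alone can induce a correlation

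*Protocol article*

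**What the plan says.** All references are to the protocol article.

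- **Analysis planned (Statistical analysis).** "Correlations between changes in GIS scale results and EGG parameter findings will also be analyzed". The method follows a paragraph later: "Correlations between the GIS scale and EGG parameters will be analyzed by Pearson's correlation coefficients or by Spearman's Rho". No partial, stratified or arm-adjusted version is named, and neither sentence says which patients enter.
- **Surrounding text (Statistical analysis).** The sentence just before the first quote compares EGG parameters before and after treatment in the two groups. The next paragraph puts every analysis on an intention-to-treat basis.
- **Expected effect (Hypothesis).** BST is expected to improve dyspeptic symptoms, and "6 weeks of oral administration of BST can improve the abnormal frequency and power parameters on cutaneous EGG".
- **How the question is framed elsewhere.** The abstract's Background asks about a correlation "between changes in gastric myoelectrical activity and improvement in dyspeptic symptoms during" administration of the formula. The main Background asks whether "the changes in GMA recorded by cutaneous EGG before and after the oral administration of BST can reflect the clinical efficacy of BST". The Discussion expects that "the improvement in dyspeptic symptoms after the oral administration of BST may be assessed by measuring the changes in cutaneous EGG parameters".
- **Timing (abstract, Methods).** "Cutaneous electrogastrography will be performed and assessed at baseline and at 6 weeks".

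**The concern.** The second of the two stated aims is to learn how EGG recordings relate to symptoms and whether EGG can provide biological evidence of BST's efficacy. The abstract and the Discussion say that the correlations will be used to judge whether cutaneous EGG has a clinical application in FD.

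That use needs an association between patients: those whose EGG improves more should also improve more in symptoms. A coefficient pooled over both arms mixes this with something else. If BST shifts the mean of both measures, the arms form two displaced clouds, and a line through both slopes even when there is no relation inside either cloud. Arm is then a common cause of both changes. The artefact appears under the trial's own hypothesis, so a pooled coefficient would be hardest to interpret if the treatment works as hoped.

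**Working it through.** **Inputs**

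- From Statistical analysis: GIS difference Δ = 3.5, σ = 5.37, two-sided α = 5%, power 80%, allocation 1:1, dropout 25%, total 100.
- Not in the article: the effect of BST on any EGG parameter. I assume a standardised effect d2 from 0 to 0.8 SD.
- Assumed null: zero correlation between GIS change and EGG change within each arm, with normal data.

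**The plan's own figure**

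n per arm = 2 × [5.37 × (1.960 + 0.842) / 3.5]² = 36.95, rounded up to 37. Then 37 / 0.75 = 49.3, rounded up to 50 per arm, 100 in total. Both stated figures reproduce. The two sample sizes used below are therefore N = 74 (2 × 37, after the assumed dropout) and N = 100 (all randomised).

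**Correlation induced by arm alone**

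Standardised GIS effect: d1 = 3.5 / 5.37 = 0.652.

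In a pooled 1:1 sample, arm contributes d1·d2/4 to the covariance and d²/4 to each variance, so

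r = (d1·d2/4) / √[(1 + d1²/4)(1 + d2²/4)].

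With d2 = 0.652: d1·d2/4 = 0.1062, and r = 0.1062 / 1.1062 = 0.096.

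With d2 = 0.2: r = 0.0326 / √(1.1062 × 1.01) = 0.031.

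**Rejection rate of the nominal 5% Pearson test** (20,000 simulated trials per setting)

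| EGG effect d2 (assumed) | Induced r | Pooled, N = 100 | Pooled, N = 74 |
|---|---|---|---|
| 0 | 0 | 4.7% | 4.8% |
| 0.2 | 0.031 | 6.2% | 5.8% |
| 0.35 | 0.053 | 8.4% | 7.4% |
| 0.5 | 0.075 | 11.6% | 10.1% |
| 0.652 | 0.096 | 16.0% | 12.4% |
| 0.8 | 0.115 | 20.9% | 16.9% |

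The arm-adjusted partial correlation rejects in 4.8% to 5.2% of trials in every row, and a correlation within the BST arm alone in 4.8% to 5.3%. Spearman gives no protection: at N = 100 and d2 = 0.652 its pooled rate is 15.5%.

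**Size against the critical value**

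Significance needs |r| of about 0.20 at N = 100 and 0.23 at N = 74. Every induced r in the table is well below that. Even in the last row at N = 100, 100 − 20.9 = 79.1% of trials show no significant correlation.

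**The case against.** **Pooling is never stated.** A reader might infer that the plan commits to a pooled coefficient. The documents do not support that. A correlation computed within one arm needs no arm term, so naming Pearson or Spearman does not show a fault. The abstract, Background and Discussion all speak of change under BST, which can be read as the BST arm only, and there arm cannot confound. This stands as a possible reading, but it does not settle the matter. The article also uses the administration of BST as a label for the trial period in both arms: under Primary outcome it times the GIS assessments this way, and under Safety it times tests on all participants this way. The two-group sentence and the intention-to-treat statement leave pooling open.

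**An article may leave this to the full protocol or SAP.** This is fair for fine detail. Here, though, the article does name the method, and the method as named has no arm term.

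**The size rests on an assumed EGG effect.** This stands. At 0.2 SD the excess is about one percentage point, and at zero there is none. The article lists about six EGG quantities. The inflation applies only to those that BST actually shifts, and nothing says which these are.

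**Rejecting is an error only against a within-arm null.** This also stands. When both means shift, the pooled correlation truly is non-zero, and covariation produced by treatment is arguably part of asking whether EGG reflects BST's efficacy. But it would not show that EGG tracks an individual patient's response, which is what clinical use of EGG would require.

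**Baseline correlations are unaffected.** Correct. Symptom severity against EGG at baseline precedes treatment.

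**Conclusion.** The point holds conditionally. The article plans the change-change correlation with unadjusted coefficients and leaves open whether the arms are pooled. If they are pooled and BST improves both measures, arm alone induces r of about 0.03 to 0.12, and the nominal 5% test rejects in about 6% to 21% of trials at N = 100 (about 6% to 17% at N = 74). This assumes zero within-arm correlation, the planned GIS effect of 0.65 SD, and an EGG effect of 0.2 to 0.8 SD that the article does not give.

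The stronger conclusion, that a treatment effect would by itself be expected to yield a significant correlation, does not follow: the induced r lies below the critical value throughout, and most trials would not reach significance from it alone. The primary outcome and the listed secondary outcomes are untouched. Priority is low to moderate: the analysis is exploratory, but it serves a stated aim and the remedy is almost free.

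**What to change.** For the change-change analysis, state that the association is estimated as a partial correlation adjusted for treatment arm, or by regressing GIS change on EGG change with arm in the model. Report the coefficient within each arm beside it, which also shows whether the two arms agree. Do not rest the conclusion about clinical use of EGG on an unadjusted pooled coefficient. If only the BST arm was meant, say so; that removes this particular problem. Leave the baseline symptom–EGG correlations as they are.

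The cost is a sentence or two of analysis wording, one degree of freedom (N − 3 in place of N − 2) and a little more analysis. No new data are needed. The within-arm coefficients will be less precise, since each rests on 37 to 50 patients.
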